## Abstract

**Background:**

ST-segment elevation myocardial infarction (STEMI) is a clinically distinguishable yet lethal sequela of ischaemic heart disease (IHD). In sub-Saharan Africa (SSA), death due to acute STEMI is increasing. In South Africa, there is a paucity of data available on the clinical outcomes of acute STEMI within one year for individuals treated in the public healthcare sector. This study primarily seeks to determine the one-year all-cause mortality rate of acute STEMI. The study also assesses the value of serum cardiac biomarkers of myocardial damage and serum uric acid in predicting all-cause mortality in STEMI.

**Methods:**

This is a single-centre observational prospective cohort of all consecutive individuals presenting with an acute STEMI to the Charlotte Maxeke Johannesburg Academic Hospital (CMJAH) in Johannesburg, South Africa. Research data will be sourced on admission through electronic medical records, blood laboratory results and coronary angiography reports, and at follow-up through periodic telephonic interviews and standardised echocardiograms. At least 355 eligible participants will be continuously followed over one year, and clinical outcomes will be measured 30 days, three months, six months and one year after the index hospitalisation.

**Discussion:**

This study provides insights into the demographic, risk factors and clinical profiles of individuals with STEMI in South Africa. Its findings may improve the risk stratification, prognostication, and therapeutic management of STEMI patients in our setting. By comparing the clinical outcomes between the different coronary reperfusion strategies, our results may guide clinicians in providing better patient treatment, particularly in sub-Saharan Africa, where access to percutaneous coronary intervention may be limited. Furthermore, the study offers insights into the routine use of baseline serum uric acid as a potential low-cost prognostic biomarker of all-cause mortality in STEMI. Finally, this study’s findings may be of public health significance to local policymakers to aid in reinforcing primary prevention strategies and developing structured referral networks for timely coronary reperfusion of acute STEMI.

**Supplementary Information:**

The online version contains supplementary material available at 10.1186/s12872-023-03416-3.

## Background

There has been considerable developments in the last 15 years in the treatment of ST-segment elevation myocardial infarction (STEMI), more particularly the timelines to reperfusion therapy, the application of emergent primary percutaneous coronary intervention (PPCI), the widespread shift away from streptokinase use to tissue plasminogen activators, the implementation of a pharmaco-invasive strategy, advances in antiplatelet therapy and cardiac rehabilitation [1].

An acute STEMI is a fatal and clinically distinguishable sequela of ischaemic heart disease (IHD). In the absence of contraindications, the treatment of choice for a STEMI is prompt reperfusion by percutaneous coronary intervention (PCI) or timeous thrombolytic therapy [2].

Unlike in high-income countries (HIC), where STEMI-related deaths are declining, in sub-Saharan Africa (SSA), STEMI mortality is on the rise [3, 4]. Moreover, in SSA, death due to cardiovascular diseases has superseded death due to communicable diseases [5]. Although the in-hospital mortality rate of STEMI has been reported in SSA, data on outpatient follow-up in this population is primarily confined to HIC. This study aims to determine the clinical outcomes in STEMI patients within a year of treatment at the Charlotte Maxeke Johannesburg Academic Hospital (CMJAH).

This research is significant due to the paucity of contemporary data on the one-year clinical outcomes of STEMI patients treated in South Africa. Notably, the consequential prevalence of HIV infection and tuberculosis in our setting will provide a unique insight into the relationship between these disease processes, the biomarkers of myocardial damage and the clinical outcomes within a year of an acute STEMI presentation .

Data from the South African Registry of Acute Coronary Events multinational Survey of current management Strategies (ACCESS) reported that the thirty-day and one-year outpatient all-cause mortality rates in STEMI patients were 2.4% and 6.7%, respectively [6]. The French Registry on Acute ST-elevation Myocardial Infarction (FAST-MI) of 2008 reported that in patients treated with thrombolysis, the thirty-day mortality rate is 9.2% without PCI and 3.9% when rescue PCI is subsequently performed (p = 0.044) compared to 2.8% in those who undergo a pharmaco-invasive approach (p = 0.147) [7]. According to the FAST-MI of 2008, the crude one-year survival rate is 78.5% in patients without reperfusion, 93.6% for thrombolysis, and 91.8% for PPCI (p < 0.001 for overall comparison; p = 0.31 for thrombolysis vs PPCI). When compared to other regions in SSA, the crude one-year mortality rate of 6.7% reported in the South African ACCESS registry was lower than the overall death rate of 10.4% reported in a single national referral centre study conducted in the Intensive Care Unit of Abidjan Heart Institute, in Côte d’ Ivoire [8].

An age of ≥ 70 years, female gender and heart failure on admission are significant factors predictive of mortality at thirty days and one-year follow-up of STEMI, irrespective of myocardial revascularisation strategy [8]. Diabetes mellitus on admission and a history of stroke or transient ischaemic attack (TIA) are also associated with a higher risk of death at one year [6]. In SSA, delayed access to emergency medical services (EMS) and healthcare facilities with reperfusion therapy limits favourable outcomes in STEMI patients [9]. In a local prospective cohort study at a single tertiary centre involving 100 STEMI patients, Meel et al. reported that only 37% of eligible patients received fibrinolytic therapy [10]. Only 3% received the medication within one hour. The median total time delay to administering a fibrinolytic agent was 270 min (45–584), with patient and transport delays being the most crucial reasons. For fibrinolytic therapy not given within one hour of hospital arrival, the calculated number of lives lost due to these delays was 32 patients per 1000 treated.

The Thrombolysis in Myocardial Infarction (TIMI) risk score for STEMI is a bedside risk assessment tool that predicts 30-day crude mortality [11]. This score is based on eight clinical variables obtained from the clinical history, physical examination, electrocardiogram (ECG) and laboratory testing. The score ranges from 0 to 14. The 30-day mortality is 0.8% with a score of zero and 35.9% with scores greater than eight (p < 0.001).

The Global Registry of Acute Coronary Events (GRACE) risk score for STEMI predicts the six-month risk of crude mortality. This score involves eight variables from the clinical history, physical examnation, ECG and laboratory testing, and it stratifies patients into three risk categories (low risk: < 109 points, moderate risk: 109–140 points, and high risk: > 140 points). The recently adopted GRACE risk score 2.0 predicts the risk of death one year or three years after a STEMI but substitutes the Killip class and serum creatinine with diuretic usage and a history of renal dysfunction, respectively. The median predicted one-year mortality risks of low, moderate and high-risk groups are 1.6%, 2.8% and 5.9%, respectively [12].

In addition, discontinuation of evidence-based medication (such as aspirin, beta-blockers, statins and angiotensin-converting enzyme inhibitors) one month beyond hospitalisation is associated with higher twelve-month mortality (hazards ratio, 3.81; 95% CI 1.88–7.72; p < 0.001) [13].

Serum cardiac biochemical markers (biomarkers) of myocardial damage and atherosclerosis, including high-sensitivity cardiac troponin T and I (hs-cTnT and hs-cTnI), C - reactive protein (CRP), and serum uric acid (SUA), have proven to be helpful for prognostication in STEMI patients.

Admission serum hs-cTnT or hs-cTnI is strongly predictive of death, non-fatal AMI and revascularisation at 30 days (hazard ratio 5.16, 95% CI 2.25–11.9, p < 0.001) and one year (hazard ratio 2.88, 95% CI 1.79–4.63, p < 0.001), even after adjusting for baseline risk factors such as age, sex, race and time from symptom onset to index hs-cTnT or I measurement [14].

Treatment guidelines recommend measuring serum CRP to aid in diagnosing and treating STEMI patients. STEMI patients with serum CRP > 3.0 mg/dL at or after discharge have a significantly higher risk of re-infarction, ischaemic stroke, coronary artery occlusion and death within two years of the index AMI [15]. The risk of mortality increases with higher CRP values at admission (Odds Ratio 1.04, 95% CI 0.91–1.20, p < 0.0001) and 30 days (Odds Ratio 1.12, 95% CI 0.93–1.34, p = 0.007) after hospital discharge [16].

In a systematic review and meta-analysis involving nine studies, Trkulja et al. showed that ‘high’ baseline SUA independently predicts all-cause mortality, re-infarction, angina, revascularisation and cardiac arrest at 30 days (Odds Ratio 2.26, 95% CI 1.85–2.77, p < 0.001), and at both 6 and 12 months (Hazard Ratio 1.30, 95% CI 1.01–1.68, p = 0.042) [17]. ‘High’ SUA refers to values in the hyperurecaemic, i.e., > 0.42 mmol/L and > 0.36 mmol/L or high-normal range, i.e., 0.31 mmol/L-0.42 mmol/L and 0.25 mmol/L -0.36 mmol/L in men and women, respectively. However, this study provided no data on the association between serial measurements of SUA at 30 days, six months and one year after hospital discharge and clinical outcomes in STEMI patients. Moreover, the combination of these three serum cardiac biomarkers might have an incremental value in the risk stratification of these patients.

Primary percutaneous coronary intervention (PPCI) is emergent PCI without prior fibrinolysis. It is the current reperfusion strategy of choice in STEMI patients who present within 12 h of symptom onset, provided it is conducted expeditiously within 120 min from the time of STEMI diagnosis [4]. A study by Zhu et al. showed that PPCI significantly reduces mortality, non-fatal re-infarction, and stroke by approximately 50% at 6 to 12 months (Odds Ratio 0.52, 95% CI 0.44–0.62, p < 0.001) [18].

However, fibrinolysis remains an important alternative reperfusion strategy that prevents early mortality in 30 per 1000 patients treated within 6 h after symptom onset. Fibrinolytic therapy should be administered within 12 h of symptom onset, provided that early primary PCI cannot be performed and there are no contraindications [19].

Facilitated PCI refers to routine early PCI < 12 h after reperfusion with either fibrinolysis or glycoprotein IIb/IIIa (GPIIb/IIIa) receptor inhibitors, regardless of the pharmacologic reperfusion outcome [20]. The Strategic Reperfusion Early After Myocardial Infarction (STREAM) study has shown that adopting a pharmaco-invasive strategy (i.e., fibrinolysis followed by coronary angiography or possible rescue PCI ≥ 2 h after failed fibrinolysis) offers similar benefits in all-cause thirty-day mortality when compared with primary PCI [21]. A pharmaco-invasive approach is safer and has less risk of 30-day mortality, non-fatal re-infarction, stroke, and major bleeding than facilitated PCI and fibrinolytic therapy alone (Odds Ratio for death 0.79, 95% CI 0.59–1.08; p < 0.14 when compared to fibrinolysis) [20]. Revascularisation using either thrombolysis or a pharmaco- invasive approach is common in low-to-middle-income countries (LMIC).

The Minimising Adverse Haemorrhagic Events by Transradial Access site and systemic Implementation of AngioX: Radial vs. Femoral (MATRIX: Radial vs. Femoral) randomised controlled trial has provided robust evidence in morbidity and mortality benefits that favour the radial approach as the default vascular access site in ACS patients who undergo PCI [22]. This study showed that for the invasive management of ACS, when compared to femoral access, radial access significantly reduces the net adverse clinical events mainly through a decrease in.

major bleeding and all-cause death (Hazard ratio 0.83; 95% CI 0.74–0.96; p = 0.0092 and Hazard ratio 0.72; 95% CI 0.53–0.99; p = 0.045, respectively).

Finally, sustained optimal primary and secondary prevention therapy reduces thirty-day and one-year mortality in ACS patients. Dual antiplatelet therapy (DAPT) (i.e., a combination of aspirin and P2Y12 inhibitors such as clopidogrel, ticagrelor or prasugrel) is recommended for all STEMI patients. DAPT, oral beta-blockers and angiotensin-converting enzyme inhibitors decrease all-cause mortality after a STEMI [23]. High-intensity statins significantly reduce ischaemic stroke events in STEMI patients [24]. These agents prove most beneficial when initiated early in patients with no contra-indications.

This study seeks to determine the event rates of crude mortality, crude survival, re-hospitalisation, heart failure, angina, major bleeding, thromboembolism, arrhythmias and revascularisation at 30 days, three months, six months and one year after the index STEMI. We seek to compare these clinical outcomes between four primary STEMI sub-groups (i.e., those who receive fibrinolysis vs. no fibrinolysis vs. PCI vs. no PCI) in our local practice and compared with those reported in HIC and other regions of SSA. We also aim to evaluate the association between the peak baseline measurements of serum hs-cTnT, serum CRP, SUA and clinical outcomes within a year.

We hypothesise that the thirty-day and one-year crude mortality rates for STEMI patients observed in our setting would follow similar trends to those in HIC with no significant differences. We anticipate that the various STEMI management therapies provided in our practice would offer similar one-year all-cause mortality and morbidity benefits, irrespective of the revascularisation strategy used when comparing fibrinolysis vs. PPCI vs. fibrinolysis followed by PCI among groups. In our setting, we expect that advanced age, female gender, diabetes mellitus and heart failure on admission play critical roles in predicting death at 30 days and one year.

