## Methods

### Study aims

This study aims to determine the clinical outcomes of an acute STEMI within one year of clinical presentation to the division of cardiology at the CMJAH. The study also evaluates the association between baseline serum cardiac biomarkers of myocardial infarction and all-cause mortality within a year of acute STEMI.

The primary objective is:

To determine the all-cause mortality rate of an acute STEMI at 30 days, three and six months, and one year after the index presentation.

The secondary objectives include:

To determine the rates of cardiac-related re-hospitalisation, heart failure, angina, major bleeding, thromboembolism, non-fatal arrhythmias (namely, atrial fibrillation, ventricular tachycardia, and complete heart block) and planned or unplanned repeated revascularisation at 30 days, three and six months and one year after the index STEMI at CMJAH.To assess the relationship between all-cause mortality and the peak serum hs-cTnT, CRP and SUA measured on admission.To describe the baseline clinical characteristics of STEMI patients in our setting.To compare the clinical outcomes between STEMI patients who received thrombolysis, PCI, a pharmaco-invasive strategy and those who underwent no reperfusion at 30 days, six and three months, and one year after the index STEMI.To determine the baseline clinical predictors of all-cause mortality at 30 days, three months, six months and one year after the initial STEMI.To describe the adjuvant medical care provided and medication compliance rates at 30 days, three months, six months and one year after the index discharge from the hospital.

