### Study design and setting

The study is a single-centre, observational, prospective cohort of all consecutive individuals with an acute STEMI diagnosis presenting to the CMJAH. The study will take place in the division of cardiology at the CMJAH, a academic state-owned tertiary PCI-capable healthcare facility in Johannesburg, South Africa. Participants will be followed over one year, and clinical outcomes will be measured at 30 days, three months, six months and one year from the index date of hospital discharge. The first day after hospitalisation will be considered day one of the follow-up.

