### Data collection

Research data will be collected from 01 May 2021 to 30 October 2022. The Primary Investigator (PI) will use the Research Electronic Data Capture (REDCap) software as the primary data collection tool. At baseline, the PI will capture demographic, clinical, calculated TIMI and GRACE scores, laboratory test results, ECG, echocardiographic, coronary angiographic, revascularisation and discharge medication data shown in Appendix B. The PI will create and access a reference list of the study participants’ hospital numbers and specific study numbers. The PI will retrieve these from the relevant progress notes, National Health Laboratory Service (NHLS) lab track, electronic medical records, and coronary angiogram report database of the division of cardiology at CMJAH.

The PI will telephonically contact all participants or their designated family members to monitor general well-being, medication compliance, outpatient cardiac clinic visits and cardiac-related re-admissions. When re-admitted to CMJAH, the PI will access the relevant hospital records to ascertain whether our study’s outcomes of interest occurred. Participants will be deemed compliant with medication if they say so during the telephonic interviews. The telephonic interviews will follow a closed-ended structured questionnaire, as depicted in Appendix C. Each participant will receive a telephonic interview call at 30 days, three months, six months and twelve months after the index hospital discharge date. All participants will be given the PI’s phone number and business card and encouraged to save the number on their cellphones when they sign informed consent forms so that doctors from other hospitals can contact the PI for cardiac-related referrals to CMJAH.

The PI will obtain the peak values of serum hs-cTnI, serum CRP and SUA from routine blood tests drawn at baseline for all participants. Automated messages generated through REDCap will be sent to remind both the PI and the participants of their scheduled outpatient clinic visits a week before the visits.

An experienced research sonographer will perform standardised echocardiograms during the outpatient clinic visits three months and one year after the index discharge. The two cardiologists who supervise the study will verify all echocardiograms. Appendix D shows the left ventricular parameters and valve analysis that will be recorded.

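### The article gives two time origins for outcomes, index STEMI or presentation versus hospital discharge, so it is not fixed whether bleeding, arrhythmia and thromboembolism in the reperfusion admission count

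*Protocol article*

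**What the plan says.** The objectives start the clock at the acute event:

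- The Background lists the non-fatal outcomes, among them "major bleeding, thromboembolism, arrhythmias and revascularisation at 30 days, three months, six months and one year after the index STEMI", and says they will be compared between treatment sub-groups. It then states the expectation that the strategies give similar one-year mortality and morbidity benefit.
- Study aims sets the overall aim as the "clinical outcomes of an acute STEMI within one year of clinical presentation". The primary mortality objective also runs from the index presentation.
- The secondary objective on non-fatal outcomes ends with "planned or unplanned repeated revascularisation at 30 days, three and six months and one year after the index STEMI at CMJAH". The one comparing reperfusion groups ends with "those who underwent no reperfusion at 30 days, six and three months, and one year after the index STEMI".

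The Methods start the clock at discharge:

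- Study design and setting measures clinical outcomes, without distinguishing fatal from non-fatal, from the date of discharge, and adds: "The first day after hospitalisation will be considered day one of the follow-up".
- Data collection schedules all four telephone interviews from the discharge date. Its one sentence on searching records for outcomes begins "When re-admitted to CMJAH, the PI will access the relevant hospital records to ascertain whether".
- For the index stay, Data collection names baseline data groups (demographic, clinical, risk scores, laboratory, ECG, echocardiography, angiography, revascularisation, discharge medication) and refers to Appendix B. None of the named groups is in-hospital complications.

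The Abstract is ambiguous: "clinical outcomes will be measured 30 days, three months, six months and one year after the index hospitalisation" could refer to the start or the end of the hospital stay.

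**The concern.** The outcomes at issue include major bleeding, thromboembolism, atrial fibrillation, ventricular tachycardia and complete heart block. Any of these that occurs between reperfusion and discharge falls inside the window set by the objectives and outside the window set by Study design and setting. Two analysts working from different sections would count different events in the same patients.

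This matters most for the comparison of reperfusion strategies. Early harm from a strategy is part of what such a comparison should show. The article's own evidence on strategies is of this kind: "A pharmaco-invasive approach is safer and has less risk of 30-day mortality, non-fatal re-infarction, stroke, and major bleeding than facilitated PCI". If the index stay is left out, a difference that arises there cannot appear in the result, and the stated expectation of similar morbidity becomes easier to support. The planned comparison with rates from high-income countries and other African regions also needs a matching clock.

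**Working it through.** **No figure to reproduce.** The article gives no in-hospital or post-discharge rate for bleeding, arrhythmia or thromboembolism. The sample sizes of 355 and 182 do not depend on this point. The check is therefore a side-by-side reading, followed by algebra for the direction of any distortion.

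**Step 1: where the clock starts.**

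| Section | Origin | Index-stay events inside the window? |
|---|---|---|
| Abstract, Methods | index hospitalisation | unclear |
| Background, closing paragraphs | index STEMI | yes |
| Study aims, overall aim and primary objective | presentation | yes |
| Study aims, non-fatal outcomes and reperfusion comparison | index STEMI | yes |
| Study design and setting | discharge; day one is the day after the stay | no |
| Data collection, interviews | discharge | no |

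**Step 2: what the discharge clock does to a 30-day rate.** Let L be the length of stay in days. Counted from presentation, the window covers days 0 to 30. Counted from discharge, it covers days L to L + 30. The discharge window loses days 0 to L and adds days 30 to L + 30. It also contains only patients discharged alive. Such a rate is not comparable with a 30-day rate counted from presentation.

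**Step 3: direction for the comparison.** For two strategies, let a1 and a0 be the risks of an event during the stay, and b1 and b0 the risks after discharge. Ignore repeat events and in-hospital deaths. Then

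- from discharge: RR = b1/b0
- from presentation: RR = (a1 + b1)/(a0 + b0) = w × (a1/a0) + (1 − w) × (b1/b0), with w = a0/(a0 + b0).

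The discharge-based ratio lies nearer to 1 than the presentation-based ratio when the strategies differ more during the stay than afterwards, in the same direction. If the two ratios are equal, the risk ratio does not change. If the difference lies mainly after discharge, the distortion runs the other way.

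**Step 4: illustration with assumed rates.** None of these rates is in the article.

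- Stay risk 4% versus 2%, later risk 1% in both: (4 + 1)/(2 + 1) = 1.67 from presentation; 1/1 = 1.0 from discharge.
- Stay risk 8% versus 2%, later risk 1% in both: (8 + 1)/(2 + 1) = 3.0 from presentation; 1/1 = 1.0 from discharge.
- Stay risk 4% versus 2%, with the same ratio of 4/2 = 2 later, so 2 × 1% = 2% versus 1%: (4 + 2)/(2 + 1) = 2.0 from presentation; 2/1 = 2.0 from discharge.

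In the first two lines the discharge-based 1.0 is an input, because equal later risks were assumed. The lines show how the distortion works. They do not estimate it for this study.

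**The case against.** The strongest reply is that the formal objectives already settle the matter. They run from the index STEMI or presentation, and a reader could treat the discharge wording as a description of the call schedule. This stands in part: it shows that exclusion of index-stay events is not a settled rule. It does not remove the conflict, because Study design and setting applies the discharge origin to the clinical outcomes themselves and defines day one to match.

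A second reply is that the article is condensed. Appendix B is not shown, and the Discussion says the outcomes of the reperfusion therapies are outlined in the data collection appendices. The investigator already opens progress notes, electronic records and angiography reports for the index stay, and the re-admission sentence does not claim to be the only source of outcomes. This stands. The absence of in-hospital complications from the named data groups is not evidence that they go unrecorded. Even so, recording an event at baseline would not make it an outcome event under the discharge rule.

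A third reply concerns the horizon. The similarity hypothesis is about one year, and one-year morbidity includes re-hospitalisation, which can only follow discharge, as well as angina, heart failure and repeat revascularisation, which can accrue throughout the year. This also stands. The effect on an overall one-year comparison may be smaller than on 30-day bleeding or arrhythmia.

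A reader might infer that index-stay events never enter the comparison, or that the plan confirms similar morbidity by construction. The documents support neither reading. The first takes one side of a contradiction as decided, and the second needs event rates that the article does not give.

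**Conclusion.** The time origin is contradictory within the article and must be reconciled. This is an error in what is stated, not a detail left to an analysis plan. If the discharge rule is followed as written, major bleeding, arrhythmia and thromboembolism during the reperfusion admission are not outcome events. The comparison of strategies can then be pulled towards no difference, on the condition that the strategies differ more during the stay than after it. The 30-day rates would not be comparable with rates counted from presentation whether or not that condition holds. The size cannot be computed from the documents.

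The discharge wording covers deaths as well, so the primary mortality objective, which runs from presentation, meets the same conflict. For the non-fatal outcomes the point bears on secondary objectives, and correction is advisable because it is cheap and removes a possible bias.

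**What to change.** 1. Make index presentation the single time origin in the Abstract, Background, Study aims, Study design and setting, and Data collection. The aim and the primary objective already use it. State that index-stay events count.
2. In Data collection, say that major bleeding, thromboembolism, arrhythmia and heart failure during the index stay are taken from the hospital records already opened for baseline data. Keep conditions present on arrival as baseline. If Appendix B already has these fields, refer to it and say that they feed the outcomes.
3. Report each outcome for the in-hospital period, for the period after discharge, and combined. Base the reperfusion comparison on the combined count.
4. The interviews can stay scheduled from discharge, provided event dates are recorded. A call 30 days after discharge never comes earlier than 30 days after presentation, so dated events can be placed on the presentation clock.

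The cost is wording in five sections, at most a few REDCap fields, and a little more abstraction. Reported event rates will be higher. Because the source is the index hospital record, the events can also be abstracted for participants already enrolled.

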#### Characteristics of study participants

All consecutive patients presenting to CMJAH with an acute STEMI diagnosis will be invited to participate in the study as shown in the flow diagram provided in Appendix A.

Inclusion criteria include:

Age ≥ 18 years.All confirmed acute STEMI diagnoses as per the fourth universal definition of myocardial infarction, i.e., myocardial injury evidenced by a rise and/or fall of serum cardiac troponin levels with at least one value above the 99th percentile of the upper reference limit, in the presence of the following, ischaemic symptoms and new ischaemic ECG changes, i.e., persistent ST-segment elevation of at least 1 mm measured from the J-point in at least two contiguous leads, or new pathological Q-waves or a new-onset left bundle branch block.All confirmed STEMI receiving the various STEMI management, i.e., thrombolysis, PCI, pharmaco-invasive approach, and no reperfusion.Able to give written informed consent.The participant or participant’s next of kin is reachable by cellphone.

Exclusion criteria include:

ACS other than STEMI, i.e., NSTEMI and unstable angina.Unable to give consent.Unreachable by telephone call (participant or their next of kin).Incomplete medical records.

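### The reperfusion groups are listed in three non-matching ways, one of them overlapping, and grouping by treatment received from the index STEMI would favour the PCI-based groups unless the time origin is settled

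*Protocol article*

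**What the plan says.** All references are to the protocol article. It describes the comparison groups in three ways.

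- **Background, aims paragraph:** "four primary STEMI sub-groups (i.e., those who receive fibrinolysis vs. no fibrinolysis vs. PCI vs. no PCI".
- **Background, hypothesis paragraph (the next one):** "comparing fibrinolysis vs. PPCI vs. fibrinolysis followed by PCI among groups". There is no unreperfused group, and PCI without prior fibrinolysis appears only as primary PCI.
- **Study aims, secondary objective:** "patients who received thrombolysis, PCI, a pharmaco-invasive strategy and those who underwent no reperfusion". Characteristics of study participants repeats these categories: "thrombolysis, PCI, pharmaco-invasive approach, and no reperfusion".

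Statistical analysis plans crude Kaplan-Meier curves by reperfusion group, compared by log-rank test, without pointing to one of these lists. Chi-square tests are planned for categorical variables.

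The only description of a pharmaco-invasive strategy is in the Background, in the account of a cited trial: "fibrinolysis followed by coronary angiography or possible rescue PCI ≥ 2 h after failed fibrinolysis".

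The time origin also varies. In Study aims, mortality is counted from the index presentation and the comparison of strategies from the index STEMI. In Study design and setting, outcomes are timed from hospital discharge, with day one on the first day after hospitalisation.

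**The concern.** There are two separate problems.

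First, chi-square, ANOVA and log-rank tests need each patient in exactly one group. The list called primary in the Background does not meet this, and the other two lists match neither it nor each other. The differences move patients. Someone given fibrinolysis and then angiography without PCI fits the Background description of pharmaco-invasive, but is not in a group of fibrinolysis followed by PCI. A non-lysed patient with PCI that was not primary fits the Study aims label but not the hypothesis label.

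Second, Study aims assigns patients by what they received. If time runs from the index STEMI, a lysed patient must survive to angiography or PCI to count as pharmaco-invasive, and a non-lysed patient must survive to the procedure to count as PCI. Earlier deaths default to thrombolysis or no reperfusion. This is immortal-time bias, and nothing in the planned crude Kaplan-Meier comparison corrects it. The article expects similar benefit across strategies and says the comparison may guide clinicians, so a spurious difference would bear on both.

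**Working it through.** No figure in the plan needs reproducing. The stated sample sizes do not enter the argument, apart from using 355 as the cohort size in step 1.

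**1. Overlap.** Everyone is in fibrinolysis or no fibrinolysis, and again in PCI or no PCI. So 355 patients give 2 × 355 = 710 entries in a four-row table.

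A four-row chi-square for a binary outcome uses 3 degrees of freedom and the 5% critical value 7.815. With these rows the statistic is the sum of two 2×2 chi-squares, one per factor. If the factors are independent, that sum has 2 degrees of freedom, and the true rejection rate is exp(−7.815/2) = 0.020.

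A simulation agrees. It used N = 355, 6.7% mortality in everyone (the one-year figure cited in the Background), and assumed independent shares of 37–50% for fibrinolysis and 40–60% for PCI, with 20,000 runs per setting.

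| Grouping | Rejection at nominal 5% |
|---|---|
| Overlapping list | 1.9–2.1% |
| Four disjoint cells (both, fibrinolysis only, PCI only, neither) | 4.6–4.9% |

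The test is miscalibrated, and conservative in these settings.

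**2. Treatment received, clock from the index STEMI.** All inputs are assumed, since the documents give none: 200 lysed patients; a proportion e die before angiography or PCI is possible; 60% of survivors go on to PCI; later mortality is 4% whether or not they do. There is no treatment effect.

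- Early deaths E = 200e; survivors S = 200 − E.
- Thrombolysis alone: n = E + 0.4S; deaths = E + 0.4S × 0.04.
- Pharmaco-invasive: 4.0% by construction.

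| e | E | S | n, thrombolysis alone | Deaths | Mortality | Pharmaco-invasive |
|---|---|---|---|---|---|---|
| 2% | 4 | 196 | 82.4 | 7.14 | 8.7% | 4.0% |
| 3% | 6 | 194 | 83.6 | 9.10 | 10.9% | 4.0% |
| 5% | 10 | 190 | 86.0 | 13.04 | 15.2% | 4.0% |

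**3. Second set of assumptions.** One-year mortality m = 10%; PCI planned for a share s of 50–70%; a proportion e of 1–4% die before the planned time; PCI has no effect. Mortality is (m − e)/(1 − e) in the pharmaco-invasive group and [(1 − s)m + se]/[(1 − s) + se] in the rest.

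- s = 0.5, e = 0.01: 0.0909/0.1089 = 0.83
- s = 0.7, e = 0.02: 0.0816/0.1401 = 0.58
- s = 0.7, e = 0.04: 0.0625/0.1768 = 0.35

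The true ratio is 1.0 throughout.

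**4. What shrinks it.** If follow-up starts after hospitalisation, deaths before an in-hospital procedure are outside the clock. Step 2 then gives 4.0% in both groups and step 3 a ratio of 1.0. Only PCI after discharge could still produce the bias. The consent criterion acts in the same direction. If, as an assumption, it removed half of the six early deaths in the 3% row, thrombolysis alone would have (3 + 3.10)/(3 + 77.6) = 6.10/80.6 = 7.6%.

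**The case against.** A reader might infer that all the planned group tests are invalid. The documents do not support that. The overlapping list is in the Background. The Methods give four categories, repeated in the eligibility criteria, that read naturally as disjoint if thrombolysis means thrombolysis alone and PCI means PCI without prior fibrinolysis. Statistical analysis ties no test to the overlapping list. What stands is that it ties the log-rank test to no list at all, while the overlapping one is called primary.

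A reader might also infer a rule of classifying by whatever treatment was eventually given. No such rule is stated. It would be an inference from the absence of a membership window, which a condensed article may leave to the full protocol. What is stated is grouping by treatment received, with a clock from the index STEMI.

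The strongest objection concerns that clock. Study design and setting starts follow-up after hospitalisation, which removes the in-hospital mechanism, and patients who die before they can give written consent are never enrolled. Both points stand and make the bias conditional. They do not dispose of it, because the article's own comparative objective uses the other origin.

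The illustration in step 2 counts only patients who go on to PCI as pharmaco-invasive, whereas the Background description would also admit angiography alone. That objection is fair. Counting angiography would enlarge that group and shrink thrombolysis alone, so the early deaths would weigh more there.

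Finally, it is tempting to see the same bias in the cited registry contrast, where "the thirty-day mortality rate is 9.2% without PCI and 3.9% when rescue PCI is subsequently performed". The article does not say how that registry assigned groups or set time zero, so nothing can be drawn from it.

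**Conclusion.** The concern holds in a limited form. The mismatch between the three lists and the overlap in the one called primary are plain from the text. A chi-square or log-rank test across the overlapping list would be invalid, with rejection near 2% at a nominal 5% in the settings simulated, which assume independent factors.

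The bias towards the PCI-based groups follows from the Study aims wording only if time runs from the index STEMI. On that clock it could be material: 10.9% against 4.0% with no true effect, with 8.7% to 15.2% against 4.0% over the early-death range tried, and spurious mortality ratios of 0.83 to 0.35 under the second set of assumptions. These are illustrations, not estimates for this cohort. With follow-up starting after hospitalisation, the in-hospital part is zero and only post-discharge PCI remains. A statement that early deaths will fall into the non-PCI groups would therefore go further than the documents allow.

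The comparison is a secondary objective, so the change should be made, but the primary mortality estimate does not depend on it.

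**What to change.** - Replace the overlapping list in the Background with one mutually exclusive set, and use the same set in the hypothesis, Study aims, the eligibility criteria and Statistical analysis.
- Reconcile the time origin between Study aims and Study design and setting, and name the one used for the Kaplan-Meier and log-rank comparison.
- For analysis, assign patients by initial reperfusion strategy at presentation: primary PCI, fibrinolysis, or no initial reperfusion. Non-lysed patients who have PCI later stay in the last group.
- Analyse angiography or PCI after fibrinolysis as a time-dependent covariate in a Cox model (off before the procedure, on after it) or from a stated landmark. State whether angiography alone qualifies.

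The cost is mainly wording. Procedure dates should be obtainable from the coronary angiography reports, already listed as a source under Data collection. The modelling becomes slightly more complex. Confounding by indication remains, since rescue PCI follows failed fibrinolysis. The article already acknowledges unmeasured confounding, and this change does not remove it.
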